**Confounding variable set:**

- Age

**Potential effect modifiers:**

- Age
- Asthma/COPD status
- Antihypertensive Use
- ASA Score

The directed acyclic graph below describes the assumed causal relationship between allergen trigger and primary organ failure.

**Set of confounders**

**Allergen trigger**

**Primary organ failure**

## Sensitivity Analyses

A sensitivity analyses will be conducted that uses multiple imputation to handle missing data if there is >10% missing data in the analysis model. The results will be compared to a complete case analysis.

We will also present the unadjusted estimate (i.e. unadjusted odds ratio) for the analysis of the primary outcome.

## Subgroup Analyses

As an exploratory analysis, we will also estimate the effect of allergen trigger on primary organ failure in the following subgroups:

- Age <18 vs 18+ years
- Age <40 (including children) vs 40 or above

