## Adjustment for Multiplicity

No formal adjustments for multiplicity of testing will be applied, with results interpreted based on the magnitude of the estimates and the 95% confidence intervals (CIs) rather than focussing on p-values.

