# Analysis of the Primary Outcome

## Primary Analysis

*Causal effect of allergen exposure trigger on primary organ failure*

The analysis will include allergen trigger as the exposure variable of interest and primary organ failure (defined as whether the primary organ failure was upper airway, bronchospasm, or cardiovascular) as the outcome in three models (where each type of organ failure is a separate outcome). We will fit a logistic regression model, adjusted for the set of confounders listed below, and estimate an adjusted odds ratio reported with its 95% confidence interval (CI) and p-value. If we identify effect modifiers, an adjusted marginal odds ratio will be reported, estimated following model fitting using g-computation. We will also report the number and percentage meeting the outcome in each exposure group. Since the exposure variable has multiple categories, we will present each pairwise odds ratio.

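### The age-subgroup plan gives trigger effects within strata but no estimate of how they differ by age, and some of its cells are too sparse for odds ratios.

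*Combined protocol and SAP*

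**What the plan says.** The SAP, under Subgroup Analyses, states: "As an exploratory analysis, we will also estimate the effect of allergen trigger on primary organ failure in the following subgroups". Two splits follow: "Age <18 vs 18+ years" and "Age <40 (including children) vs 40 or above". The section names no model, no trigger-by-age term, no test or estimate of the difference between strata, and no rule for empty or very small cells.

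Three other places bear on it:

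- **SAP, Primary Analysis.** There are three logistic models, one per organ failure type, and the trigger has four categories: "Since the exposure variable has multiple categories, we will present each pairwise odds ratio". On effect modification: "If we identify effect modifiers, an adjusted marginal odds ratio will be reported, estimated following model fitting using g-computation". How a modifier would be identified is not stated.
- **SAP, "Potential effect modifiers".** Age is first on the list.
- **SAP, Adjustment for Multiplicity.** "No formal adjustments for multiplicity of testing will be applied", and interpretation is to rest on estimates and confidence intervals more than on p-values.

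By contrast, the SAP's analysis of deaths per year does specify an exposure-by-time interaction term.

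**The concern.** The usual reason for showing an effect in younger and older patients is to ask whether it differs. The plan yields one odds ratio per stratum and leaves the comparison to the reader. If the strata differ in size, the smaller one has the wider interval, and a common effect can look present in one stratum and absent in the other.

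The conditional step in the Primary Analysis does not fill the gap. A marginal odds ratio from g-computation averages over age, so it does not say how the effect changes with age.

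The two splits are also not independent evidence. Those under 18 are all within the under-40 stratum, and those aged 40 or above are all within the 18+ stratum. Agreement between the splits partly reflects the same deaths counted twice.

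Finally, some planned subgroup odds ratios rest on very few events or none, and the plan does not say what will be reported there.

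**Working it through.** **Inputs.** Bronchospasm: insect 9/37, drug 68/115 (Table S2a). Cardiovascular: food 0/58, insect 21/37, drug 40/115 (Table S2b). Upper airway: drug 7/115, insect 7/37, food and contrast not reportable (Table S2c), hence under five each by the disclosure note above Table S3. The documents give no age distribution by trigger, so the younger share f is an assumption.

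**1. Reproducing the printed figures.** With odds ratio = ad/(bc) and SE(log OR) = √(1/a + 1/b + 1/c + 1/d):

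- Bronchospasm, insect v drug: (9 × 47)/(28 × 68) = 0.222, SE 0.428, CI 0.096 to 0.514, as printed.
- Cardiovascular, insect v drug: 2.461 (1.156 to 5.237), SE 0.385, as printed.
- Upper airway, insect v drug: 3.600 (1.171 to 11.067), SE 0.573, as printed.

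**2. How many subgroup odds ratios.** 3 outcomes × 6 contrasts × 4 strata = 72.

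**3. Why a common effect can look like an age effect.** If the risks are the same in both strata, the SE is about 0.428/√f in the younger stratum and 0.428/√(1 − f) in the older. At f = 20%, with log OR = −1.504 in both:

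- younger: SE 0.957, z = 1.57, CI 0.03 to 1.45;
- older: SE 0.479, z = 3.14, CI 0.09 to 0.57.

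The typical result is one interval that includes 1 and one that does not, around the same odds ratio.

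A simulation adds sampling variation. Stratum sizes were binomial with share f, true risks were 9/37 and 68/115 in both strata, tests were Wald at two-sided 5%, and there were 200,000 samples per row. Percentages are of all samples.

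| f | one stratum significant, the other not | not estimable in at least one stratum | interaction test significant |
|---|---|---|---|
| 10% | 51% | 44% | 1.5% |
| 20% | 61–62% | 16% | 2.6% |
| 30% | 51% | 6% | 3.0% |
| 40% | 41% | 3% | 3.3% |

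**4. Food-cardiovascular.** Zero of 58 overall means zero in every stratum. Three food contrasts × 4 strata = 12 odds ratios with no finite maximum-likelihood estimate. Table S2b already marks the three overall ones as inestimable.

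**5. Upper airway.** Each split has 4 triggers × 2 strata = 8 cells. Seven drug events cannot fill two cells of five, so at least one drug cell is below five. The same holds for insect. Food and contrast are under five in total, so both cells of each are below five. The minimum is 1 + 1 + 2 + 2 = 6 of 8. The 24 upper-airway odds ratios rest on at most 7 + 7 + 4 + 4 = 22 events.

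**6. What an interaction estimate could deliver.** SE of the log ratio of odds ratios = SE_overall/√(f(1 − f)). For bronchospasm at f = 50%: 0.428/0.5 = 0.856. The ratio detectable with 80% power is exp[(1.960 + 0.842) × 0.856] ≈ 11.

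| insect v drug | detectable ratio, f = 50 / 25 / 10% | power for a three-fold ratio, f = 50 / 25 / 10% |
|---|---|---|
| Bronchospasm | 11 / 16 / 54 | 25 / 20 / 12% |
| Cardiovascular | 9 / 12 / 36 | 30 / 23 / 13.5% |
| Upper airway | 25 / 41 / 211 | 16 / 13 / 8% |

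**The case against.** The strongest reply is that the plan already limits the damage. The subgroups are labelled exploratory, the SAP de-emphasises p-values, and no subgroup results appear in the documents. Counting strata as significant or not is therefore not the plan's own yardstick. This stands as a limit on severity. But a reader who follows the plan's advice and looks at intervals still has no interval for the difference between ages, which is the quantity of interest.

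A second reply is that an interaction test would be weak. That is true, as the last table shows. It favours reporting the ratio with its interval, which displays the weakness, over an informal comparison, which hides it.

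Some stronger readings are tempting but not supported:

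- A reader might infer that the strata being compared overlap. They do not: each split is disjoint, and only the two alternative cut-points share deaths.
- A reader might infer that separate models will be fitted. That is a natural reading, but the section names no model.
- A reader might conclude that the analysis cannot show a difference by age. Disjoint strata give independent log odds ratios, from which a ratio can be formed. The gap is that the plan does not specify it.
- A reader might take cells under five to mean that most upper-airway odds ratios cannot exist. Five is a disclosure limit. Table S2c prints overall odds ratios for food and contrast on such counts. If all triggers share a younger share of 5% to 50% and food and contrast have 1 to 4 events each, about 5.9 to 11.2 of 12 per split are expected to be estimable, counting those with an event for both triggers. If event ages differ sharply by trigger, the number could be far lower.

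The zero food-cardiovascular count is also a result, which the SAP's authors could not have known. A general rule for empty cells could still have been written in advance.

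**Conclusion.** The point holds as a minor one. The plan specifies within-stratum effects for two overlapping age splits and no between-stratum comparison, and nothing else in the SAP supplies one.

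For the one contrast examined, a common effect gives a one-clear, one-unclear pattern in about 41% to 61% of samples, against under 4% for a direct interaction test. These figures assume younger shares of 10% to 40%, the same share for insect and drug deaths, and no adjustment. They illustrate the risk and do not describe a result.

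Two statements need no assumption about ages: all 12 food-cardiovascular subgroup odds ratios are inestimable, and at least 6 of 8 upper-airway cells per split hold fewer than five events. Upper-airway subgroup odds ratios would therefore be very imprecise, and some may not be estimable. How many cannot be said from the documents.

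**What to change.** In the SAP's Subgroup Analyses section:

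1. Add a trigger-by-age interaction to the full-sample logistic model, with age continuous or in the plan's existing two-level splits. Three age bands would be sparser still, notably for food in bronchospasm, where 55 of 58 are events.
2. For bronchospasm, and for cardiovascular without food, report the joint interaction test and the ratio of odds ratios with its 95% CI. Base any statement about age differences on that ratio.
3. For upper airway and food-cardiovascular, give counts only where the disclosure condition above Table S3 permits, with no subgroup odds ratios.

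If a two-level split is the only age term, the interaction model is saturated and its stratum odds ratios equal those from separate fits. What it adds is the ratio with its interval.

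The cost is a few lines of SAP text and a small re-run. The downside is precision: power for a three-fold ratio is about 8% to 30% across the three outcomes (about 12% to 30% for the two retained). The analysis stays exploratory, and a null interaction must not be read as equal effects.

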# Secondary Outcomes

## 6.1 Main Analysis

All secondary objectives will be analysed as descriptive objectives and will not adjust for any confounders.

One objective is to compare the following outcomes between patient allergen exposure including:

1. Time to symptoms from allergen exposure (***ordinal outcome***).
2. Time to symptom onset to severe symptoms (***continuous outcome***).
3. Time to severe symptoms to cardiorespiratory arrest (***continuous outcome***).
4. Time to arrest to death (***ordinal outcome***).
5. Whether the patient required tracheal intubation (***binary outcome***).
   1. If required tracheal intubation, the timing of tracheal intubation (***nominal outcome***).
   2. Time to tracheal intubation from cardiorespiratory arrest among those not already intubated in theatre (***continuous outcome***).
6. Whether the patient experienced vomiting or aspiration (***binary outcome***).
7. Whether the patient received cardioversion (***binary outcome***).
8. Change in posture (***nominal outcome***).
9. Frequency of deaths per year over time by (i) allergen exposure and by (ii) age group (<18, 18-40, 40-50, 50-60, >60 (***count outcome***).

Another objective is to compare primary organ failure by the following complications:

1. Difficult airway
2. FONA (front of neck access)
3. Vomiting or aspiration
4. Pneumothorax (dichotomised to none OR one+/- both sides)
5. Cardioversion

Binary outcomes will be analysed using a similar approach to that described for the primary outcome. The unadjusted odds ratio will be estimated using a logistic regression model, reported with its 95% CI and p-value. We will also report the number and percentage meeting the outcome in each exposure group.

Continuous outcomes will be summarised by exposure group using mean and standard deviation. The unadjusted mean difference will be estimated using a linear regression model with robust standard errors, reported with its 95% CI and p-value. If the outcome appears skewed, we will instead estimate a median difference using quantile regression.

Count outcomes will be summarised by exposure group for each time point (i.e. reporting the number of deaths in each year by exposure). The adjusted incidence rate ratio will be estimated using Poisson regression, reported with the 95% CI and p-value. Given that we suspect that the rate of death is not constant over time, an exposure x time interaction term will be included in the model. If there is evidence of non-constant rate over time, we will present the marginal adjusted incidence rate ratio. If there is any evidence of overdispersion, we will instead use negative binomial regression to estimate the incidence rate ratios.

Nominal outcomes will be compared between exposure group by using cross-tabulations. If there are >5 expected counts in each cell, we will use the Chi-Square test as a measure of association.

**6.2 Sensitivity Analyses**

A sensitivity analyses will be conducted that uses multiple imputation to handle missing data if there is >10% missing data in the analysis model.

**Primary Outcome Complete Analysis**

Primary outcome complete analysis vs multiple imputation analysis is published for statistical completeness and transparency but shows little difference in the significance or strength of results.

**Table S2a**: Summary of overall average causal effect of allergen exposure on primary organ failure (bronchospasm)

| **Exposure or Contrast** | **Number (%) with bronchospasm as primary organ failure** | **Complete case analysis** | | **Multiple imputation** | |
| --- | --- | --- | --- | --- | --- |
|  |  | **Odds ratio (95% CI)** | **p-value** | **Odds ratio (95% CI)** | **p-value** |
| **Drug** | 68/115 (59.1%) |  |  |  |  |
| **Insect** | 9/37 (24.3%) |  |  |  |  |
| **Food** | 55/58 (94.8%) |  |  |  |  |
| **Contrast** | 13/27 (48.1%) |  |  |  |  |
| **Adjusted estimates (causal effects)** | | | | | |
| **Insect v Drug** | - | 0.178 (0.071 to 0.448) | <0.001 | 0.185 (0.073 to 0.466) | <0.001 |
| **Food v Drug** | - | 1.980 (0.653 to 6.008) | 0.226 | 2.867 (0.641 to 12.827) | 0.167 |
| **Contrast v Drug** | - | 0.339 (0.130 to 0.887) | 0.028 | 0.445 (0.168 to 1.175) | 0.101 |
| **Food v Insect** | - | 11.137 (3.038 to 40.826) | <0.001 | 15.530 (3.166 to 76.186) | 0.001 |
| **Contrast v Insect** | - | 1.909 (0.536 to 6.803) | 0.317 | 2.410 (0.648 to 8.964) | 0.187 |
| **Contrast v Food** | - | 0.171 (0.044 to 0.671) | 0.012 | 0.155 (0.027 to 0.901) | 0.038 |
| **Unadjusted estimates (associations)** | | | | | |
| **Insect v Drug** | - | 0.222 (0.096 to 0.514) | <0.001 | 0.222 (0.094 to 0.528) | 0.001 |
| **Food v Drug** | - | 12.672 (3.741 to 42.924) | <0.001 | 12.399 (3.615 to 42.528) | <0.001 |
| **Contrast v Drug** | - | 0.642 (0.277 to 1.489) | 0.302 | 0.585 (0.253 to 1.353) | 0.209 |
| **Food v Insect** | - | 57.037 (14.298 to 227.535) | <0.001 | 55.731 (13.904 to 223.378) | <0.001 |
| **Contrast v Insect** | - | 2.889 (0.996 to 8.379) | 0.051 | 2.631 (0.905 to 7.644) | 0.075 |
| **Contrast v Food** | - | 0.051 (0.013 to 0.202) | <0.001 | 0.047 (0.012 to 0.185) | <0.001 |

**Table S2b**: Summary of overall average causal effect of allergen exposure on primary organ failure (cardiovascular)

| **Exposure or Contrast** | **Number (%) with cardiovascular as primary organ failure** | **Complete case analysis** | | **Multiple imputation** | |
| --- | --- | --- | --- | --- | --- |
|  |  | **Odds ratio (95% CI)** | **p-value** | **Odds ratio (95% CI)** | **p-value** |
| **Drug** | 40/115 (34.8%) |  |  |  |  |
| **Insect** | 21/37 (56.8%) |  |  |  |  |
| **Food** | 0/58 (0.0%) |  |  |  |  |
| **Contrast** | 12/27 (44.4%) |  |  |  |  |
| **Adjusted estimates (causal effects)** | | | | | |
| **Insect v Drug** | - | 2.920 (1.208 to 7.055) | 0.018 | 3.076 (1.296 to 7.305) | 0.011 |
| **Food v Drug** | - | Cannot be estimated | N/A | Cannot be estimated | N/A |
| **Contrast v Drug** | - | 1.589 (0.668 to 3.781) | 0.293 | 1.503 (0.612 to 3.691) | 0.371 |
| **Food v Insect** | - | Cannot be estimated | N/A | Cannot be estimated | N/A |
| **Contrast v Insect** | - | 0.544 (0.178 to 1.667) | 0.285 | 0.489 (0.157 to 1.516) | 0.213 |
| **Contrast v Food** | - | Cannot be estimated | N/A | Cannot be estimated | N/A |
| **Unadjusted estimates (associations)** | | | | | |
| **Insect v Drug** | - | 2.461 (1.156 to 5.237) | 0.019 | 2.591 (1.238 to 5.422) | 0.012 |
| **Food v Drug** | - | Cannot be estimated | N/A | Cannot be estimated | N/A |
| **Contrast v Drug** | - | 1.500 (0.641 to 3.511) | 0.350 | 1.535 (0.646 to 3.648) | 0.331 |
| **Food v Insect** | - | Cannot be estimated | N/A | Cannot be estimated | N/A |
| **Contrast v Insect** | - | 0.610 (0.224 to 1.656) | 0.332 | 0.592 (0.212 to 1.655) | 0.316 |
| **Contrast v Food** | - | Cannot be estimated | N/A | Cannot be estimated | N/A |

**Table S2c**: Summary of overall average causal effect of allergen exposure on primary organ failure (Upper airway)

| **Exposure or Contrast** | **Number (%) with upper airway as primary organ failure** | **Complete case analysis** | | **Multiple imputation** | |
| --- | --- | --- | --- | --- | --- |
|  |  | **Odds ratio (95% CI)** | **p-value** | **Odds ratio (95% CI)** | **p-value** |
| **Drug** | 7/115 (6.1%) |  |  |  |  |
| **Insect** | 7/37 (18.9%) |  |  |  |  |
| **Food** | NR |  |  |  |  |
| **Contrast** | NR |  |  |  |  |
| **Adjusted estimates (causal effects)** | | | | | |
| **Insect v Drug** | - | 3.534 (0.927 to 13.468) | 0.064 | 3.610 (1.186 to 10.991) | 0.024 |
| **Food v Drug** | - | 2.946 (0.393 to 22.082) | 0.292 | 2.113 (0.277 to 16.150) | 0.468 |
| **Contrast v Drug** | - | 6.935 (2.183 to 22.032) | 0.001 | 2.565 (0.566 to 11.621) | 0.220 |
| **Food v Insect** | - | 0.834 (0.127 to 5.486) | 0.849 | 0.585 (0.079 to 4.343) | 0.598 |
| **Contrast v Insect** | - | 1.962 (0.560 to 6.881) | 0.291 | 0.711 (0.131 to 3.844) | 0.690 |
| **Contrast v Food** | - | 2.354 (0.329 to 16.828) | 0.392 | 1.214 (0.098 to 15.087) | 0.879 |
| **Unadjusted estimates (associations)** | | | | | |
| **Insect v Drug** | - | 3.600 (1.171 to 11.067) | 0.025 | 3.083 (1.129 to 8.416) | 0.028 |
| **Food v Drug** | - | 0.842 (0.209 to 3.382) | 0.808 | 0.632 (0.156 to 2.566) | 0.520 |
| **Contrast v Drug** | - | 1.234 (0.242 to 6.303) | 0.800 | 1.494 (0.317 to 7.041) | 0.610 |
| **Food v Insect** | - | 0.234 (0.056 to 0.971) | 0.045 | 0.205 (0.050 to 0.847) | 0.029 |
| **Contrast v Insect** | - | 0.343 (0.065 to 1.801) | 0.206 | 0.485 (0.098 to 2.387) | 0.371 |
| **Contrast v Food** | - | 1.467 (0.230 to 9.333) | 0.685 | 2.363 (0.379 to 14.722) | 0.356 |

**Association of complications with primary outcome and allergen trigger category**

As a condition of ethics approval, death counts of less than five cannot be directly reported. Where this has occurred in tabular reporting, we have abbreviated this to Not Reportable (NR).

**Table S3:** Association between complication and primary organ failure

|  | **Number (%) with specified primary organ failure** | **Number (%) without specified primary organ failure** | **Complete case analysis** | | **Multiple imputation** | |
| --- | --- | --- | --- | --- | --- | --- |
|  |  |  | **Odds ratio (95% CI)** | **p-value** | **Odds ratio (95% CI)** | **p-value** |
| **Primary Organ Failure: Bronchospasm** | | | | | | |
| **Difficult airway** | 21/29 (72.4%) | 101/160 (63.1%) | 1.533 (0.639 to 3.680) | 0.338 | 1.523 (0.668 to 3.473) | 0.316 |
| **Cricothyroidotomy** | 5/13 (38.5%) | 122/193 (63.2%) | 0.364 (0.115 to 1.155) | 0.086 | 0.380 (0.130 to 1.117) | 0.078 |
| **Vomiting or aspiration** | 37/53 (69.8%) | 116/197 (58.9%) | 1.615 (0.842 to 3.098) | 0.149 | 1.774 (0.944 to 3.334) | 0.075 |
| **Pneumothorax** | 11/18 (61.1%) | 129/209 (61.7%) | 0.975 (0.363 to 2.617) | 0.959 | 1.014 (0.363 to 2.835) | 0.979 |
| **Cardioversion** | 26/41 (63.4%) | 32/46 (69.6%) | 0.758 (0.310 to 1.853) | 0.544 | N/A | N/A |
| **Primary Organ Failure: Cardiovascular** | | | | | | |
| **Difficult airway** | NR | 53/160 (33.1%) | 0.150 (0.034 to 0.653) | 0.011 | 0.206 (0.053 to 0.807) | 0.024 |
| **Cricothyroidotomy** | NR | 55/193 (28.5%) | 0.753 (0.200 to 2.839) | 0.675 | 0.974 (0.273 to 3.475) | 0.967 |
| **Vomiting or aspiration** | 12/53 (22.6%) | 61/197 (31.0%) | 0.653 (0.321 to 1.328) | 0.239 | 0.618 (0.313 to 1.220) | 0.165 |
| **Pneumothorax** | 5/18 (27.8%) | 60/209 (28.7%) | 0.955 (0.326 to 2.796) | 0.933 | 0.992 (0.344 to 2.858) | 0.988 |
| **Cardioversion** | 12/41 (29.3%) | 12/46 (26.1%) | 1.172 (0.457 to 3.005) | 0.740 | N/A | N/A |
| **Primary Organ Failure: Upper airway** | | | | | | |
| **Difficult airway** | 6/29 (20.7%) | 6/160 (3.8%) | 6.696 (1.990 to 22.531) | 0.002 | 3.401 (1.126 to 10.269) | 0.030 |
| **Cricothyroidotomy** | 5/13 (38.5%) | 16/193 (8.3%) | 6.914 (2.023 to 23.629) | 0.002 | 5.530 (1.627 to 18.804) | 0.006 |
| **Vomiting or aspiration** | NR | 20/197 (10.2%) | 0.722 (0.236 to 2.212) | 0.569 | 0.653 (0.216 to 1.971) | 0.449 |
| **Pneumothorax** | NR | 20/209 (9.6%) | 1.181 (0.253 to 5.513) | 0.832 | 1.133 (0.206 to 6.232) | 0.886 |
| **Cardioversion** | NR | NR | 1.737 (0.276 to 10.948) | 0.557 | N/A | N/A |

**Table S4:** Association between complication and allergen exposure

|  | **Number (%) with complication among those with allergen exposure** | **Number (%) with complication among those without allergen exposure** | **Complete case analysis** | | **Multiple imputation** | |
| --- | --- | --- | --- | --- | --- | --- |
|  |  |  | **Odds ratio (95% CI)** | **p-value** | **Odds ratio (95% CI)** | **p-value** |
| **Allergen Exposure: Drug** | | | | | | |
| **Difficult airway** | 14/134 (10.4%) | 13/103 (12.6%) | 0.808 (0.362 to 1.803) | 0.602 | 0.931 (0.421 to 2.058) | 0.860 |
| **Cricothyroidotomy** | 5/141 (3.5%) | 7/112 (6.2%) | 0.551 (0.170 to 1.787) | 0.321 | 0.630 (0.211 to 1.880) | 0.406 |
| **Vomiting or aspiration** | 19/179 (10.6%) | 39/172 (22.7%) | 0.405 (0.223 to 0.734) | 0.003 | 0.411 (0.228 to 0.740) | 0.003 |
| **Pneumothorax** | 17/161 (10.6%) | 10/162 (6.2%) | 1.794 (0.795 to 4.049) | 0.159 | 1.857 (0.826 to 4.175) | 0.134 |
| **Cardioversion** | 34/56 (60.7%) | 17/55 (30.9%) | 3.455 (1.577 to 7.566) | 0.002 | N/A | N/A |
| **Allergen Exposure: Food** | | | | | | |
| **Difficult airway** | 6/51 (11.8%) | 21/186 (11.3%) | 1.048 (0.399 to 2.751) | 0.925 | 0.853 (0.334 to 2.177) | 0.739 |
| **Cricothyroidotomy** | NR | 10/203 (4.9%) | 0.804 (0.171 to 3.792) | 0.783 | 0.561 (0.114 to 2.764) | 0.477 |
| **Vomiting or aspiration** | 26/64 (40.6%) | 32/287 (11.1%) | 5.452 (2.934 to 10.132) | 0.000 | 5.295 (2.876 to 9.749) | 0.000 |
| **Pneumothorax** | NR | 23/264 (8.7%) | 0.762 (0.253 to 2.293) | 0.629 | 0.698 (0.235 to 2.069) | 0.516 |
| **Cardioversion** | 6/21 (28.6%) | 45/90 (50.0%) | 0.400 (0.142 to 1.124) | 0.082 | N/A | N/A |
| **Allergen Exposure: Insect** | | | | | | |
| **Difficult airway** | 5/24 (20.8%) | 22/213 (10.3%) | 2.285 (0.776 to 6.724) | 0.134 | 1.679 (0.571 to 4.938) | 0.344 |
| **Cricothyroidotomy** | 5/28 (17.9%) | 7/225 (3.1%) | 6.770 (1.988 to 23.057) | 0.002 | 5.302 (1.512 to 18.586) | 0.009 |
| **Vomiting or aspiration** | 7/63 (11.1%) | 51/288 (17.7%) | 0.581 (0.250 to 1.348) | 0.206 | 0.546 (0.236 to 1.264) | 0.158 |
| **Pneumothorax** | NR | 23/263 (8.7%) | 0.745 (0.248 to 2.241) | 0.601 | 0.756 (0.253 to 2.263) | 0.617 |
| **Cardioversion** | 3/20 (15.0%) | 48/91 (52.7%) | 0.158 (0.043 to 0.577) | 0.005 | N/A | N/A |
| **Allergen Exposure: Contrast** | | | | | | |
| **Difficult airway** | NR | 25/209 (12.0%) | 0.566 (0.127 to 2.531) | 0.457 | 0.676 (0.165 to 2.776) | 0.586 |
| **Cricothyroidotomy** | 0/34 (0.0%) | 12/219 (5.5%) | Cannot be estimated | N/A | N/A | N/A |
| **Vomiting or aspiration** | 6/45 (13.3%) | 52/306 (17.0%) | 0.751 (0.303 to 1.867) | 0.538 | 0.747 (0.299 to 1.866) | 0.532 |
| **Pneumothorax** | NR | 25/280 (8.9%) | 0.498 (0.114 to 2.180) | 0.354 | 0.508 (0.114 to 2.261) | 0.374 |
| **Cardioversion** | 8/14 (57.1%) | 43/97 (44.3%) | 1.674 (0.540 to 5.193) | 0.372 | N/A | N/A |

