**1.0 Study Synopsis**

## Primary Objectives

To examine differences in primary organ failure that develop in patients who have fatal anaphylaxis after being exposed to different allergen trigger categories. We define patient allergen exposure to one of four categories of allergens: drug, insect, food, and radiocontrast, where ‘drug’ will be the reference group.

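### For vomiting/aspiration and cardioversion, Table S4 sets each allergen against the other three pooled, where the SAP implies pairwise odds ratios with drug as reference

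*Combined protocol and SAP*

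**What the plan says.** **Reference group.** The SAP synopsis, under Primary Objectives, defines four allergen categories and states that drug "will be the reference group".

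**Contrasts.** The Primary Analysis section adds: "Since the exposure variable has multiple categories, we will present each pairwise odds ratio".

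**Binary secondary outcomes.** Section 6.1 says: "Binary outcomes will be analysed using a similar approach to that described for the primary outcome". It then specifies the model: "The unadjusted odds ratio will be estimated using a logistic regression model, reported with its 95% CI and p-value". It also sets their status: "All secondary objectives will be analysed as descriptive objectives and will not adjust for any confounders".

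**Which complications are planned by allergen.** The Secondary Objectives and section 6.1 list vomiting/aspiration and cardioversion among the outcomes to be compared across allergen groups. Difficult airway, front of neck access and pneumothorax appear only in the separate list to be compared with primary organ failure.

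**What was reported.** Tables S2a to S2c give six pairwise contrasts per outcome. Table S4 has one block per allergen, with one column for deaths with that allergen and a second headed "Number (%) with complication among those without allergen exposure". It contains no pairwise contrast and gives no reason for the different layout.

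**The concern.** In a one-against-rest layout, the comparator is a different mixture in every block. If one allergen is extreme, it pulls the comparator in the other three blocks. Those blocks then show odds ratios away from 1 that say little about the allergen named in the block heading.

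Two readings are at stake. A reader of the drug block sees significantly less vomiting or aspiration and may take this as a feature of drug anaphylaxis. A reader interested in cardioversion cannot find the contrasts the plan points to, because the pooled comparators blur them. The SAP asks for results to be interpreted on the size of the estimates and their 95% intervals, and these are the quantities that the changing comparator alters.

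**Working it through.** **Inputs.** Complete-case counts printed in Table S4. Cells marked NR are not used.

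| | Drug | Insect | Contrast | Food |
|---|---|---|---|---|
| Vomiting/aspiration | 19/179 (10.6%) | 7/63 (11.1%) | 6/45 (13.3%) | 26/64 (40.6%) |
| Cardioversion | 34/56 (60.7%) | 3/20 (15.0%) | 8/14 (57.1%) | 6/21 (28.6%) |

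**Method.** With events *a* and non-events *b* in one group, and *c* and *d* in the other, OR = *ad/bc*. The 95% interval is exp[ln OR ± 1.96 × √(1/*a* + 1/*b* + 1/*c* + 1/*d*)]. For two groups this equals unadjusted logistic regression.

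**Step 1: the comparator.** For vomiting, the three non-drug denominators sum to 64 + 63 + 45 = 172 and their events to 26 + 7 + 6 = 39. These are the figures in the second column of the drug row, so the comparator is the other three pooled.

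**Step 2: the printed figure.** Drug v rest, vomiting: (19 × 133)/(160 × 39) = 0.405. The standard error is √(1/19 + 1/160 + 1/39 + 1/133) = 0.303, giving 0.223 to 0.734 and p=0.003, as printed. The other vomiting and cardioversion rows reproduce too. The arithmetic in Table S4 is sound.

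**Step 3: what drives the drug row for vomiting.** Insect plus contrast is 13/108 (12.0%). Drug against that pool is (19 × 95)/(160 × 13) = 0.87 (0.41 to 1.84), p=0.71. A chi-square test across drug, insect and contrast gives p=0.87. Drug v food is (19 × 38)/(160 × 26) = 0.17.

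**Step 4: the six pairwise odds ratios.**

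| Contrast | Vomiting/aspiration | Cardioversion |
|---|---|---|
| Food v drug | 5.76 (2.89 to 11.48) | 0.26 (0.09 to 0.77), p=0.015 |
| Insect v drug | 1.05 (0.42 to 2.64) | 0.11 (0.03 to 0.44) |
| Contrast v drug | 1.30 (0.49 to 3.46) | 0.86 (0.26 to 2.83) |
| Insect v food | 0.18 (0.07 to 0.46) | 0.44 (0.09 to 2.08) |
| Contrast v food | 0.22 (0.08 to 0.61) | 3.33 (0.81 to 13.79) |
| Contrast v insect | 1.23 (0.38 to 3.94) | 7.56 (1.49 to 38.2), p=0.015 |

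Two examples: food v drug cardioversion is (6 × 22)/(15 × 34) = 0.26, and contrast v insect cardioversion is (8 × 17)/(6 × 3) = 7.56.

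**Step 5: set against the printed one-against-rest rows.**

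| Row | Printed in Table S4 | With drug as reference |
|---|---|---|
| Insect, vomiting | 0.581 (0.250 to 1.348) | 1.05 (0.42 to 2.64) |
| Contrast, vomiting | 0.751 (0.303 to 1.867) | 1.30 (0.49 to 3.46) |
| Contrast, cardioversion | 1.674 (0.540 to 5.193) | 0.86 (0.26 to 2.83) |
| Food, cardioversion | 0.400 (0.142 to 1.124), p=0.082 | 0.26 (0.09 to 0.77), p=0.015 |

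The first three point estimates cross 1, but their intervals include 1 on both scales. The fourth keeps its direction, and its interval now excludes 1. Contrast v insect cardioversion has no counterpart in the table; the contrast row shows only p=0.372.

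**The case against.** **The plan is less explicit than it could be.** The drug reference is stated under the primary objective and the pairwise promise under the primary analysis. Section 6.1 says only that the approach is similar. This stands: pairwise reporting for secondary outcomes is an inference. It is still the natural one, since nothing in the SAP describes a one-against-rest contrast and Table S2 shows how the authors applied the wording. Calling the secondary objectives descriptive rules out confounder adjustment; it does not choose a different contrast.

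**The table is correctly labelled, and the explanation is on the page.** This stands too. Drug deaths did have less recorded vomiting than non-drug deaths, and the food row (40.6%) shows why. A reader might infer that the layout creates a false drug effect. The documents do not support that: 0.405 is right for its stated contrast, and drug does differ from food. What fails is reading the row as specific to drug.

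**Direction.** A reader might also infer that the layout reverses real associations. It does not. The three estimates that cross 1 are compatible with no difference under either comparator, and they answer different questions. Food with vomiting and insect with cardioversion keep direction and significance.

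**The drug v insect-plus-contrast figure is itself unplanned.** True. It serves only to show where 0.405 comes from; the pairwise figures carry the point.

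**Scope.** Three of the five complications have no planned comparison by allergen, so the SAP cannot be said to require pairwise results for them. This stands and limits the point to vomiting/aspiration and cardioversion.

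**The main article may report pairwise results.** This cannot be checked from the documents. It would lessen the point but would not explain the layout of Table S4.

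**Conclusion.** The point holds for vomiting/aspiration and cardioversion. Table S4 uses a contrast that the SAP does not describe, without saying so, in place of the one it most naturally implies.

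The size is moderate. One significant row, drug with vomiting, needs to be understood as a food difference. Two cardioversion contrasts whose intervals exclude 1, food v drug and contrast v insect, cannot be read from the table. The second rests on 14 and 20 deaths and is very imprecise, so its omission matters more than its exact value.

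The primary result is untouched, and these are unadjusted, descriptive analyses without multiplicity adjustment.

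The conclusion assumes that the similar approach in section 6.1 carries over the reference group and the pairwise contrasts. All figures are complete case. The documents do not allow the imputed vomiting contrasts to be recomputed, and Table S4 gives no imputed results for cardioversion.

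**What to change.** - **Vomiting/aspiration and cardioversion:** fit one unadjusted logistic model for each, with trigger as a four-level factor and drug as reference. Report all six pairwise odds ratios with 95% intervals in the Table S2 layout, for complete cases and, where already reported, for multiple imputation. Show the four group percentages side by side, with NR where the ethics condition requires it.
- **Difficult airway, cricothyroidotomy and pneumothorax:** label the allergen comparison as not pre-specified, and preferably use the same layout. Mark contrasts with an empty cell as not estimable; contrast is 0/34 for cricothyroidotomy, so three of the six contrasts there are affected.
- **If one-against-rest is kept:** present it as an unplanned addition, and note beside the drug row for vomiting that food accounts for the difference.
- **SAP section 6.1:** state outright that the drug reference and the pairwise contrasts apply to binary secondary outcomes.

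The cost is a few simple models, including re-runs on the imputed data, and one replaced supplementary table. Some intervals will be wider than the pooled ones.
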